#### CM Condition: Behavioral Counseling

Participants will receive a 5-session smoking cessation behavioral counseling program lasting approximately 15 to 20 minutes weekly. Sessions may be conducted through secure video conference or by telephone, depending on participant preference. Sessions will incorporate cognitive behavioral therapy along with motivational interviews to resolve reluctance to quit. Counseling will include health education and goal setting for smoking cessation, coping with withdrawal symptoms, relapse prevention skills, and as-needed motivational interviewing techniques to target reluctance about cessation. The recommended quit date is in week 2, after preparatory steps to quit are introduced in week 1. The behavioral protocol will be a 5-session adaptation of the VA Integrated Care for Smoking Cessation protocol [49].

#### TAU Condition

Control participants will receive usual care at the SFVAHCS: (1) referral to the Tobacco Cessation Clinic and (2) referral to the VA’s free Telephone Quitline, “TeleQuit” (known as “Quit VET”). The Tobacco Cessation Clinic is a consult service that proactively calls patients 3 times to offer pharmacological and behavioral smoking cessation treatment. Veterans will also be provided with information on accessing Quit VET, a national toll-free number available to veterans that allows them to speak with a smoking cessation counselor for up to 5 sessions [50]. At week 6, participants receiving TAU will document their participation in these interventions via self-report, and a medical chart review will be conducted to collect information regarding their engagement.

### Outcomes Evaluation

#### Primary Outcomes: Feasibility

We will evaluate feasibility by the following: (1) Recruitment rate: whether at least 25 of 36 participants (≥70% of the target sample) are enrolled within the study period. (2) Level of engagement: engagement in CM will be evaluated by the documented proportion of CO videos uploaded in weeks 2 to 5 among those randomized to CM. (3) Retention: completion rate of study measures at posttreatment among eligible participants will be assessed.

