### Study Objectives and Aims

In this pilot RCT, veteran smokers undergoing major elective surgery (n=36) will be randomized to receive the 5-week mCM protocol or 5 weeks of treatment as usual (TAU; offering VA Tobacco Cessation Clinic and VA Telephone Quitline) remotely. The mCM smoking-cessation protocol will comprise a 5-week, fixed-incentive schedule, including once-daily CM incentives contingent on bioverified abstinence, weekly behavioral coaching, and remote CO monitoring. Both groups will be offered smoking-cessation medication [21]. Our first aim (aim 1) is to develop an mCM smoking-cessation protocol to be integrated into VA surgical settings. This protocol will modify an extant CM model for smoking cessation within the VA [34] to be adapted for delivery via telehealth. Additional aims include assessing the feasibility of CM for TUD in surgical settings (aim 2) and comparing CM with TAU (exploratory aim). We predict that CM will be feasible in the surgical setting, as assessed by measures of enrollment, retention, and engagement in the CM sessions. As exploratory outcomes, we will explore the effect of CM versus TAU on smoking cessation and abstinence outcomes.

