### Recruitment and Overall Study Schedule

Participants will be recruited through (1) data queries of VA electronic health record data available through the VA Corporate Data Warehouse and (2) direct recruitment. Data queries will identify patients with an upcoming major elective surgical procedure from a predefined list. We will then identify individuals with documentation of current smoking, using an established approach via the Corporate Data Warehouse national VA database with codes, or “health factors.”

Partners in surgical subspecialties will assist with recruitment through referrals. Direct recruitment will allow the team to recruit participants with a stated interest in tobacco cessation and facilitate targeted recruitment in clinics that serve women and members of underrepresented minority groups. If recruitment rates decrease to below 2 participants per month, we will expand the eligibility criteria from major surgeries to include less invasive eye surgeries and podiatric surgeries.

The protocol eligibility criteria were developed to include participants up to 6 months prior to surgery to improve generalizability after extensive discussions with colleagues in surgery. Surgical colleagues described that some elective major surgeries (eg, some orthopedic, vascular, and neurosurgeries) may not be scheduled for months until successful smoking cessation has occurred, given the risks of cigarette smoking and impaired wound healing with some procedures. Therefore, to be as inclusive as possible to a range of participants awaiting scheduling for elective major surgery, the eligibility criteria include participants who smoke up to 6 months prior to surgery. The preoperative period varies by participant and is being tracked in this pilot study.

Once a veteran participant is recruited, we will follow the study timeline as delineated in Table 1. This schedule of enrollment, interventions, and assessments adheres to the latest SPIRIT (Standard Protocol Items: Recommendations for Interventional Trials) guidelines for reporting (Checklist 1) [35].

**Table 1. T1:** Schedule of enrollment, interventions, and assessments.

	Trial period							
	Enrollment		Postrandomization					Closeout
	Screening and baseline		Intervention phase					Follow-up
Time point (wk)	Week −4	Week 0^a^	Week 1	Week 2	Week 3	Week 4	Week 5	Week 6^a^
Time window (d)^b^	30	7±14	7	7	7	7	7	7+14
Enrollment								
Eligibility screen	✓							
Informed consent	✓							

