### Power Analysis

Because the nature of aim 2 was primarily to examine feasibility, we aimed only to observe large effects (*f*=.40) with a modest degree of power (β=.80). The results of the power analysis based on rmANOVA with α=.05 indicate that the proposed sample size (n=18 per condition) is adequate for proposed analysis (minimum n=16). Because intervention efficacy is an exploratory aim in this pilot test, we are not attempting to power the analyses for aim 3.

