## Results

### Status of This Study

This pilot trial has been funded since July 2024, and a 1-year no-cost extension has been granted through June 2027. The recruitment and data collection started in December 2025. The first participant consented on December 12, 2026. As of May 2026, 18 participants have been enrolled and randomized in this pilot trial so far. The enrollment of the last participant is expected to be in March 2027 to reach a target of 36 enrolled participants, and the data collection is expected to be completed by April 2027. There will be no interim data analysis, but preliminary analysis is expected to be completed by August 2027, and all data analyses are expected to be completed by the end of 2027.

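### The recruitment feasibility cut-off contradicts itself by one participant (25 of 36 is 69.4%, not at least 70%) and is not tied to major elective surgery

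*Protocol article*

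**What the plan says.** Under Primary Outcomes: Feasibility, the protocol article lists recruitment, engagement and retention. Recruitment is judged by "whether at least 25 of 36 participants (≥70% of the target sample) are enrolled within the study period". Engagement and retention are described as proportions to be reported, with no cut-off.

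The target population is given under Study Objectives and Aims: "veteran smokers undergoing major elective surgery (n=36) will be randomized". The Power Analysis section confirms the total of 36 as 18 per condition.

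Under Recruitment and Overall Study Schedule there is a contingency: "If recruitment rates decrease to below 2 participants per month, we will expand the eligibility criteria from major surgeries". The procedures that would be added are eye and podiatric operations of a less invasive kind. The feasibility section does not say whether people admitted that way count towards the 25.

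Status of This Study puts the start of recruitment in December 2025 and then says "The first participant consented on December 12, 2026". The next sentence reads "As of May 2026, 18 participants have been enrolled and randomized in this pilot trial so far". The abstract repeats the same dates.

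**The concern.** A success criterion written with an inequality has to give one answer for every possible result. This one is stated twice, as a count and as a percentage, and the two versions do not share a boundary. With a final enrolment of exactly 25, the authors could report either success or failure and cite the same sentence.

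The second issue is the population counted. The aim asks whether the intervention can be run in patients facing major elective surgery. If eligibility is widened because recruitment has slowed, the added participants come from outside that population, yet nothing in the criterion separates them. A shortfall in major surgery could then be made up from elsewhere and reported as feasibility in major surgery.

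The consent date is a clerical matter, but a reader who wants to work out a recruitment pace cannot do so from the dates as printed.

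**Working it through.** **Inputs.** Cut-off 25, target 36 and the 70% gloss: Primary Outcomes: Feasibility. Target of 36 as 2 × 18: Power Analysis. Start December 2025, 18 enrolled by May 2026, last enrolment expected March 2027: Status of This Study. Trigger of 2 per month: Recruitment and Overall Study Schedule.

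**1. The plan's own figure.**
- 25 / 36 = 0.694, or 69.4%. Rounded to a whole percent this is 69%, not 70%.
- 0.70 × 36 = 25.2. The smallest whole number at or above 25.2 is 26.
- 26 / 36 = 0.722, or 72.2%.

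The stated equivalence is not reproduced. Rounding 25.2 down to 25 would explain it, but an at-least rule requires rounding up.

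**2. Where the two versions disagree.**

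| Enrolled | Share of 36 | Count rule (at least 25) | Percentage rule (at least 70%) |
|---|---|---|---|
| 24 | 66.7% | fail | fail |
| 25 | 69.4% | pass | fail |
| 26 | 72.2% | pass | pass |

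They conflict at 25 and nowhere else. A label of at least 69% would match a count of 25, because 0.69 × 36 = 24.84, which rounds up to 25.

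**3. Who counts.** Side by side, the aim names major elective surgery, the contingency moves eligibility beyond major surgery, and the criterion counts participants without distinction. As an outer bound, suppose all 18 enrolled by May 2026 are major-surgery patients, the trigger then fires, and every later participant comes from the added surgeries. The count rule would be met with 18 + 7 = 25, although only 18 / 36 = 50% would belong to the target population. This shows what the wording permits; it is not a forecast.

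**4. Has the trigger been reached?** Assume first consent on 12 December 2025.
- To 31 May 2026 is 5.6 months: 18 / 5.6 = 3.2 per month.
- To 1 May 2026 is 4.6 months: 18 / 4.6 = 3.9 per month.

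Both averages are above 2 per month.

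**5. The date.** A first consent on 12 December 2026 would fall about a year after recruitment began and some seven months after 18 people had been enrolled. The year cannot be right. December 2025 fits the neighbouring sentences.

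**The case against.** The strongest reply is that this is a rounding slip worth one participant. The count comes first, the percentage is a gloss, and a reader would probably apply the count. That stands as to size, but it does not remove the ambiguity at 25.

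A second reply is that the widening of eligibility is openly prespecified and conditional, that nothing shows it has been used, and that tabulation of such participants may be left to a fuller document. This too is largely right. What remains is that the criterion, as stated here, does not say whom it counts.

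A reader might go further and infer that the rule is too lenient, because 25 participants from 12 December 2025 to 31 March 2027 (15.6 months) is 25 / 15.6 = 1.6 per month, below 2. The documents do not support that as an error:
- The figure of 2 per month triggers wider eligibility. It is nowhere declared a minimum for success, and an early-warning level stricter than a success threshold is ordinary.
- The full target over the same window is 36 / 15.6 = 2.3 per month, above the trigger.
- Few further participants are needed per month because early recruitment was quick. Counting those early participants towards a cumulative target is not a fault.
- Requiring a mean of 2 per month would raise the bar to about 2 × 15.6 = 31 participants, after 18 enrolments have been seen. That is a debatable design preference.

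A reader might also infer that the misdated consent distorts the criterion, or that the study period has been stretched to make it easier. The criterion does not use first consent as its starting point, and the extension described is of funding; the article does not say that a recruitment window used for this criterion was lengthened.

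**Conclusion.** The point holds in a limited form and is minor. The recruitment cut-off is internally inconsistent as written: 25 of 36 is 69.4%, and at least 70% requires 26. This follows from the article's own numbers without assumption, and it affects the reported result only if final enrolment is exactly 25.

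The criterion is also not confined to the population named in the aim. That has consequences only if the eligibility expansion is triggered, and the average pace to May 2026 gives no sign of it. The pace rests on reading the first consent as December 2025 and is an average, so it does not exclude a single slow month.

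The printed consent year is wrong and clerical. No finding is made on recruitment pace or leniency.

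**What to change.** 1. Make the count and percentage agree: either at least 26 of 36 (72.2%), or at least 25 of 36 with the percentage given as about 69%. The first costs one more participant to reach success; the second costs nothing. With 18 enrolled as of May 2026, neither threshold had been reached at that date, so the choice is best made and recorded before enrolment reaches 25.
2. State that the criterion is assessed on participants awaiting major elective surgery, and report anyone admitted under the eye and podiatric expansion separately. This makes the criterion slightly harder to meet if the expansion is used and changes nothing if it is not.
3. Correct the year of first consent in the abstract and in Status of This Study after checking the study records. This is an editorial correction.

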#### Primary Outcomes: Smoking Cessation

Frequency of quit attempts will be assessed using NTUS and TLFB, defined as a period of intentionally not smoking for ≥24 hours. Number of cigarettes per day will be assessed by TLFB; nicotine dependence severity will be assessed via FTND.

#### Exploratory Outcomes

Seven-day point prevalence of cigarette abstinence will be assessed post treatment, defined as (1) no smoking for 7 days prior (via TLFB) and (2) CO levels ≤6 ppm. For individuals with CO levels >6 ppm, who report smoking cannabis via TLFB and are not receiving NRT, salivary cotinine <10 ng/ml will be used [47,51]. Cutoffs are recommended by the SRNT (Society for Research on Nicotine and Tobacco) guidelines [47].

### Data Analytic Plan and Monitoring

The results will be reported using CONSORT (Consolidated Standards of Reporting Trial) guidelines [52], and analyses will be conducted using IBM SPSS and R software (R Core Team, R Foundation). Analyses will employ an intent-to-treat approach, which includes all randomized participants regardless of treatment adherence. As-treated analyses will also be conducted to examine change in smoking cessation outcomes as a function of treatment adherence. The procedure for as-treated analyses will include intervention adherence variables (ie, feedback/counseling session attendance and medication adherence) and their interactions with treatment conditions as predictors in the models. Continuous outcome variables will be checked for normality, homoskedasticity, linearity, and missingness. Descriptive analyses, repeated measures ANOVA (rmANOVA), and generalized linear mixed models (GLMMs) will be conducted to confirm study feasibility (aim 2). Descriptive analyses will include bivariate associations between demographic variables, time, and outcome variables (recruitment, engagement, and retention) via chi-squared tests, *t* tests, and correlations. rmANOVA will use time (2 levels: baseline and end-of-treatment) as the predictor. GLMMs will be used to analyze CM attendance and video uploads, in addition to intervention efficacy (aim 3*),* and posttreatment 7-day point prevalence of cigarette abstinence. Differences between treatment groups on quit attempts, mean cigarettes per day, and severity of nicotine dependence across time will be analyzed through GLMMs, with predictors of time, intervention condition, and the time-by-treatment interaction, implemented via the *lme4* and *WeMix* packages in R [53,54].

Sensitivity analyses will be used to test the influence of missing data and the assumptions related to missing data. If there is substantial missingness or attrition (>10%), we will address the missing items using multiple imputation via the *mice* package in R and conduct sensitivity analyses incorporating “inverse-probability of censoring” weights to account for attrition.

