#### Outcome Measures

##### Smoking Measures

Smoking cessation outcomes will be administered at baseline and posttreatment. A Nicotine and Tobacco Use Survey (NTUS) developed internally will assess age at first use, duration of use, use of all forms of nicotine and tobacco, prior quit attempts (ie, intentionally not smoking for ≥24 h), duration of cessation (if any), and presence of other tobacco users in the home. Posttreatment assessment will include frequency and duration of quit attempts in the past 30 days. The Fagerström Test for Nicotine Dependence (FTND) [39] is a validated instrument of the severity of physiological addiction to nicotine. The Contemplation Ladder [40] is a validated single-item measure of motivation to quit smoking. The Questionnaire of Smoking Urges [41,42] is a validated 10-item measure that assesses cigarette craving and withdrawal. It will also be administered weekly to assess craving via 1 item, *“*I have a desire for a cigarette right now,” via a scale from 0 (strongly disagree) to 100 (strongly agree) [42]. The Timeline Followback (TLFB) [43,44] is a validated, staff-administered instrument that uses anchor dates to prompt recall of substance use. It will be used to document cigarette, tobacco, electronic nicotine delivery system (ie, e-cigarette), cannabis, any other substance uses, and TUD medications. Participants who are in CM condition will be assessed at screening for past 30-day use, at weekly sessions for past 7-day or days since the last TLFB assessment, and at follow-up visit for days since the last TLFB assessment; participants who are in TAU condition will be assessed at screening for past 30-day use and at follow-up visit for days between the last TLFB assessment and follow-up assessment. Bioverification using mobile CO monitor will also be used to verify abstinence at follow-up visit. If there is inconsistency between self-report and bioverified CO level, a salivary cotinine test might be adopted as needed.

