### Other Data Documentations

A review of the VA medical record will be completed at baseline and posttreatment by staff, assessing medical conditions and treatment. Surgical complications will also be documented as adverse events (AEs). There are no restrictions on concomitant medical and mental health treatment. Concomitant medical and mental health treatment will be documented for all participants to track participants’ engagement in other interventions, and TAU participants will have their number of sessions in TAU interventions tracked.

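### The as-treated analysis is meant to examine change by adherence, but the predictors it adds have no interaction with time, so taken as written they relate adherence to the average of baseline and posttreatment

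*Protocol article*

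**What the plan says.** All the modelling text is in the protocol article, Data Analytic Plan and Monitoring.

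- Purpose: "As-treated analyses will also be conducted to examine change in smoking cessation outcomes as a function of treatment adherence".
- Main effects added for this purpose: "intervention adherence variables (ie, feedback/counseling session attendance and medication adherence".
- Product terms added alongside those main effects, given in the same sentence of the article: "and their interactions with treatment conditions as predictors in the models".
- The models that receive these additions: "Differences between treatment groups on quit attempts, mean cigarettes per day, and severity of nicotine dependence across time will be analyzed through GLMMs".
- The terms that the article lists for those models before anything is added: "with predictors of time, intervention condition, and the time-by-treatment interaction".

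On timing, Smoking Measures says: "Smoking cessation outcomes will be administered at baseline and posttreatment". Under Exploratory Outcomes, abstinence is different: "Seven-day point prevalence of cigarette abstinence will be assessed post treatment", so it has no baseline value.

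Where the section wants change by arm, it names an interaction with time. Where it wants change by adherence, it names an interaction with condition only. It states no baseline adjustment for the as-treated analysis.

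**The concern.** If the baseline value is one of the response rows, a predictor with no time interaction shifts the baseline and posttreatment rows by the same amount. Its coefficient describes a person's overall smoking level, not how that level changed. Adherence is also observed after randomization, so the term uses later behaviour to explain a value recorded before it.

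Two misreadings become possible. If lighter or less dependent smokers adhere better, the adherence term can be significant although adherence has nothing to do with change. If adherence does go with a larger fall in smoking, the term shows only half of it and may miss it. At stake is what the pilot says about whether attendance or medication use goes along with quitting.

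**Working it through.** The article gives no figure for the as-treated analysis, so there is none to reproduce. Its sample-size calculation (Power Analysis) concerns the repeated measures ANOVA and does not enter here.

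**Inputs from the article.** 18 participants per arm, alpha 0.05 (Power Analysis); two assessments, baseline and posttreatment (Smoking Measures); the model terms listed above.

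**Assumed inputs.** Outcome SD 1 at each visit, made up of participant variance 0.5 and residual variance 0.5 (baseline-posttreatment correlation 0.5); adherence standardized and, where it is related to baseline, related to the stable participant component; the size of that relation, varied from 0 to -0.4.

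**Step 1, the model as written.** With t = 0 at baseline and 1 at posttreatment, and A for adherence:

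Y = b0 + b1·t + b2·arm + b3·t·arm + b4·A + b5·A·arm + participant effect + error

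Change (posttreatment minus baseline) = b1 + b3·arm + error. A has dropped out.

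Person mean = b0 + b1/2 + (b2 + b3/2)·arm + b4·A + b5·A·arm + error. So b4 and b5 are determined by the average of the two visits.

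**Step 2, what b4 then estimates.** Let the slope on adherence be g at baseline and g + d at posttreatment, so that d is the effect on change. The slope for the mean is [g + (g + d)]/2 = g + d/2. The slope for the change is (g + d) - g = d. The listed term therefore carries all of the baseline relation g and half of d; adherence × time estimates d.

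**Step 3, no effect on change (d = 0).** The person mean has variance 0.5 + 0.5/2 = 0.75. An adherence-baseline correlation r becomes r/√0.75 with the mean: -0.23, -0.35 and -0.46 for r = -0.2, -0.3 and -0.4. Simulation, 6000 trials per row, same r in both arms, arm coded 0/1:

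| r | Listed adherence term, false positives | Adherence × time, false positives |
|---|---|---|
| 0 | 5% | 5% |
| -0.2 | 16% | 5% |
| -0.3 | 31% | 5% |
| -0.4 | 53% (54% in a repeat) | 5% |

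With arm centred, so that the term uses all 36 participants, the last three rows of the listed term rise to about 25%, 52% and 79%. If the correlation exists in the CM arm only, the listed adherence-by-condition term is falsely significant in about 16% of trials at -0.3 and 27% at -0.4; adherence × time × condition stays at about 5%.

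**Step 4, a true effect on change.** No baseline relation; adherence lowers posttreatment smoking in CM only, per SD of adherence:

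| Effect d | Listed adherence × condition: estimate, power | Adherence × time × condition: estimate, power |
|---|---|---|
| -0.5 SD | -0.25, about 12-13% | -0.50, about 28% |
| -0.8 SD | -0.40, about 24% | -0.80, about 58-59% |

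The estimates match g + d/2 and d from step 2.

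**Step 5, a second set-up.** With adherence as a yes/no variable (half adherent, arm centred, 4000 trials), a pre-existing gap of 0.5, 0.8 or 1.0 SD and no effect on change gave listed-term estimates of -0.50, -0.80 and -1.00, significant in 38%, 74% and 90% of trials. Adherence × time stayed near 0 and near 5%. A mixed model fitted to one data set of 400 per arm with a built-in gap of -0.8 gave -0.83 for the listed term and -0.05 for adherence × time.

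**Step 6, baseline adjustment instead.** Regressing the posttreatment value on baseline, arm, adherence and adherence × arm, under the null of step 3 with 0/1 coding, gave false positives for adherence in about 11% of trials at r = -0.3 and 18-19% at -0.4. A single baseline reading measures the stable level with error, so part of the gap remains.

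**The case against.** The article prints no as-treated equation. It says the procedure will include certain predictors, which need not be a complete list, and the time terms come from a later sentence about the between-arm comparison. Since the stated purpose is change, a sympathetic reader could take the adherence interactions to apply to the time-by-treatment term as well. A full analysis plan may spell this out. This lowers the weight of the point but does not remove it: the article does list the predictors, and those listed do not serve the purpose given one sentence before.

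A reader might infer something stronger: that the trial will report pre-existing differences as an adherence effect. The article does not support that. It does not say which coefficient will be interpreted, and it gives no information on how adherence relates to baseline smoking; at zero correlation the listed term keeps its 5% error rate. Nor does the point cover every smoking outcome. For seven-day abstinence, measured once, adherence and adherence-by-condition are workable predictors and no time interaction exists.

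The two-visit linear model is also a simplification. The Timeline Followback is administered weekly in CM, and quit attempts are a count that these figures do not represent.

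Finally, efficacy is exploratory and unpowered, intent-to-treat is the governing approach, and no decision rule depends on the as-treated result. All of this stands and sets the priority.

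**Conclusion.** The point holds for cigarettes per day and FTND, as a mismatch between stated purpose and stated terms. Taken as written, the listed terms measure the association of adherence with the average of baseline and posttreatment. They carry a pre-existing difference in full and a true effect on change by half.

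The halving is algebra for two visits. The false-positive rates of 16% to 54% are illustrations: they rest on assumed correlations of -0.2 to -0.4, a within-person correlation of 0.5 and a stable baseline difference. Intent-to-treat and feasibility conclusions are untouched, so this is a low-priority clarification (COULD).

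**What to change.** For cigarettes per day and FTND, state that the as-treated model adds adherence × time to time, condition, time × condition and adherence. Where adherence is measured in both arms, as medication adherence can be, also include adherence × condition and adherence × time × condition. Base the as-treated conclusion on the terms that contain time.

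Label the result associational. Adherence is not randomized, and the time terms remove only stable baseline differences, not confounding by motivation or early quitting. Do not treat a baseline-adjusted regression as interchangeable: it answers a different question and, as step 6 shows, only partly removes the problem. Leave the seven-day abstinence model as it is.

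The cost is a sentence or two and no new data. The downside is one or two extra terms in a supplementary analysis of 36 people, with correspondingly imprecise estimates.
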